
**3.12 What is the proposed sample size?: Transmission of ILI.** All calculations are based on the patient randomised (the index person). We assume that our more rigorously developed, interactive, and tailored intervention will have an NNT of at least 25 and an OR of 0.76 - very slightly better than the previous booklets which had none of these features (OR 0.80, NNT 25). There are other reasons to assume this is a reasonable (if not conservative) effect size: people who have attended with respiratory infections are slightly more likely to be interested in participating, and in this group the effect size from previous study was significantly larger; a 20% reduction in transmission is the effect size seen in most of the studies of handwashing alone; a larger effect on behaviour is also likely given the heightened public concern about ILI since the above studies. If 10% suffer ILI (<http://www.eurosurveillance.org/em/v10n12/1012-223.asp>; <http://www.niaid.nih.gov/factsheets/flu.htm>), the average household size is 2.4 individuals (<http://www.statistics.gov.uk>) i.e. 24% can be affected by the transmission of ILI either to or from the index patient, and 20% of those with no intervention will develop ILI, then 15,074 patients are needed (assuming two-sided significance level of 5% and 80% power), or 16,000 to allow some leeway in assumptions (see table below). **Transmission of RTIs.** 16000 will have greater power to detect transmission of all RTIs, and for continuous outcomes this sample size will be extremely powerful (see table). **Nested diagnostic study.** We assume that: at least 10% of the index trial cohort will report ILI, i.e. approximately 1600; 50% will agree to the virological sub study (n=800) (based on the numbers agreeing to more intensive investigation in a current microbiological study of URTI in our group); flu virus is isolated in at least 50% of individuals presenting with ILI when ILI is circulating; and that 30-50% of patients are likely to contact the doctor then in the cohort reporting ILI then we should be able to estimate the positive predictive value of a clinical diagnosis in predicting laboratory confirmed influenza with 95% confidence intervals of +/- 10% in both the sample attending the doctor (n=240-400) and the sample not attending (n=400-560). For the analysis of the likely positive and negative predictive values (of symptoms, temperature) at each stage in the illness (12hours,24hours,36 hours etc) we will have greater precision since we can use the whole sample who agree to the diagnostic study.

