
#### Range of effect sizes likely for the trial (bold= our target for that outcome)

| Effect size                                                                                                               | N per group
(with complete outcomes where
transmission of infection possible
either to or from the index person) | Total N required for ILI
(assuming 24% where transmission
possible to or from index person; and
allowing for 20% loss to follow-up) | Total N for all respiratory
infections (assuming all cohort where
transmission possible; and allowing
20% loss to follow-up) |
|---------------------------------------------------------------------------------------------------------------------------|---------------------------------------------------------------------------------------------------------------------------|----------------------------------------------------------------------------------------------------------------------------------------------|---------------------------------------------------------------------------------------------------------------------------------------|
| Dichotomous outcomes e.g. transmission
(alpha=0.05 beta=0.2)                                                   |                                                                                                                           |                                                                                                                                              |                                                                                                                                       |
| 20% vs 18% (NNT 50; OR 0.88)                                                                                       | 6039                                                                                                                      | 62,906                                                                                                                                       | 15,098                                                                                                                         |

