| 20% vs 17% (NNT 33; OR 0.82)                                                                                              | 2629                                                                                                                      | 27,386                                                                                                                                       | 6574                                                                                                                                  |
| 20% vs 16% (NNT 25 OR 0.76)                                                                                        | 1447                                                                                                                      | 15,074                                                                                                                                | 3618                                                                                                                                  |
| 20% vs 15% (NNT 20 OR 0.71)                                                                                               | 906                                                                                                                       | 9,438                                                                                                                                        | 2266                                                                                                                                  |
| Continuous outcomes e.g. days illness
(alpha=0.01 (multiple outcomes); beta=0.1)
standardised effect sizes |                                                                                                                           |                                                                                                                                              |                                                                                                                                       |

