| 0.15                                                                                                                      | 1325                                                                                                                      | 13802                                                                                                                                        | 3314                                                                                                                           |

\* standardised effect size of 0.2 = one day or less of moderately bad symptoms due to ILI or RTI

**3.13 What is the planned recruitment rate?** We will utilise the English Primary Care Research Network (PCRN) to aid with recruitment and retention. We propose recruiting this cohort over 18 months with 1 year of follow-up; this is based on our previous experience that recruiting using this mechanism 1000-1100 patients per practice should agree in under one year; 18 months will provide sufficient leeway to ensure recruitment occurs. In each practice if fewer than expected agree it will be relatively easy to select and invite more patients.

**3.14 Are there likely to be any problems with compliance?** We already have good reason to believe that patients are likely to comply, and that a trial of this size will probably find an effect; effect sizes should be larger with better development, tailoring and an interactive website.

**3.15 What is the rate of loss to follow-up?** 20% - based on our previous trials e.g. MRC ATEAM.

**3.16 How many centres will be involved?** Two centres and their local Networks (Birmingham, Southampton).

**3.17-.18. Data Entry, analysis.** Data forms will be scanned from pre printed sheets as in our previous study.

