**Main trial analysis.** The data will be analysed according to the Statistical Analysis Plan which will be approved by the Trial Steering Committee before the commencement of any analysis. One intention to treat analysis will be performed. We will assess the transmission of ILI or other respiratory tract infection - i.e. either between the index case and family members or from family members to the index person - using multiple logistic regression, the duration of symptoms labelled moderately bad days using multiple linear regression, and attendance at the GP surgery using Poisson regression, controlling for stratifiers. We found in our previous trial of leaflets there were no significant clustering effects by practice; our analysis will be based on the index patient to avoid a design effect due to family clustering. For the symptom data the main analysis will be of symptoms in the index person but a secondary analysis will assess symptoms reported for all other family members averaged at the level of the family. Confidence intervals will be reported, and the study will be reported in accordance with the CONSORT statement.

**Subgroup analysis (using two sided 1% significance levels).** We will assess whether any of the stratification variables are effect modifiers; whether age, deprivation, education level, and co-morbidities predict outcomes or are effect modifiers; whether self reported adherence to each behaviour determines outcome.

**Diagnostic study analysis.** We will assess the sensitivity specificity likelihood ratios and positive and negative predictive values for symptoms and temperature in the whole sample, and in the sub-samples who would not contact their practice or NHS Direct (either in this or in past episodes). We will use logistic regression to determine which symptoms (and or temperature) individually or in combination are most predictive. We will also estimate the predictive value of symptoms (and or temperature) for laboratory diagnosed influenza at 12 hours after the start of the illness, then at 24 hours, 36 hours, 48 hours, and 48+ hours.

**3.20 Has a pilot study been carried out?** We have not piloted this precise protocol, but have recruited very similar trial cohorts using similar recruitment mechanisms, and have developed similar websites

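### The ILI total of 13,802 for days of illness uses a 24% household transmission share that does not match the planned symptom analysis in the index person

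*Protocol*

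**What the plan says.** Protocol 3.9 and 3.10 list episodes of ILI and RTI, their duration and their transmission together as primary outcomes.

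Protocol 3.12 sizes the trial on ILI transmission. It takes 10% with ILI and a mean household of 2.4, and concludes that "24% can be affected by the transmission of ILI either to or from the index patient". The ILI column of the table carries this into every row: "assuming 24% where transmission possible to or from index person", with a further allowance for 20% loss. The continuous-outcome row (days of illness, "alpha=0.01 (multiple outcomes); beta=0.1", 0.15 SD) gives 1,325 per group, 13,802 in total for ILI and 3,314 in total for all RTIs. Of these two totals only 3,314 is in bold, the table's mark for a target. The footnote says: "standardised effect size of 0.2 = one day or less of moderately bad symptoms due to ILI or RTI".

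For the diagnostic sub-study, the same section assumes that "at least 10% of the index trial cohort will report ILI, i.e. approximately 1600". Of the planned 16,000 it says that "for continuous outcomes this sample size will be extremely powerful (see table").

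Protocol 3.17-.18 plans linear regression for duration and fixes the person analysed: "For the symptom data the main analysis will be of symptoms in the index person". Other family members' symptoms, averaged over the family, are secondary.

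**The concern.** The 24% counts households in which ILI could pass to or from the index person. It suits a transmission endpoint. For days of illness in the index person, a household where only somebody else has ILI supplies no ILI duration. The protocol's own share of index persons with ILI is 10%, so up to 14 of the 24 percentage points add nothing to an analysis of ILI duration among ill index persons.

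A reader who looks up the ILI cell sees 13,802, notes that 16,000 is larger, and concludes that ILI duration has more than 90% power at 0.15 SD. The general statement about continuous outcomes supports that conclusion. If it is wrong, an inconclusive result on ILI duration could be given more weight than the trial can bear.

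**Working it through.** **Inputs.** From Protocol 3.12 and its table: effect 0.15 SD, alpha 0.01, power 90%, ILI share 24% (10% × 2.4), at least 10% of index persons with ILI, loss 20%, planned total 16,000. From 3.17-.18: symptoms analysed in the index person. Assumed: 1:1 allocation, and a two-sided alpha for the continuous row. The text states two-sided testing for the transmission calculation ("assuming two-sided significance level of 5% and 80% power"), and a two-sided 0.01 reproduces the printed figure.

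**The plan's own figures.**
- Per group: n = 2(z₀.₉₉₅ + z₀.₉₀)² / d² = 2(2.576 + 1.282)² / 0.15² ≈ 1,323. The t-test version gives 1,324.3. The printed 1,325 is reproduced.
- Total for ILI: 2 × 1,325 / 0.24 / 0.8 = 13,802, exactly as printed. So the days-of-illness row does use the 24%.
- Power implied at 16,000: 16,000 × 0.24 × 0.8 / 2 = 1,536 per group. Then 0.15 × √(1,536/2) − 2.576 = 1.58, which is 94%. The 90% belongs to 13,802, not to 16,000.

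**Reading A: duration in index persons who had ILI.**
- Per group at 16,000: 16,000 × 0.10 × 0.8 / 2 = 640, against 1,325 required.
- Power at 0.15 SD: 0.15 × √(640/2) − 2.576 = 0.107, which is about 54%. At 13,802 (552 per group) it is about 47%.
- Power at the footnote's 0.2 SD: 0.2 × √320 − 2.576 = 1.00, which is 84%.
- Effect detectable with 90% power: (2.576 + 1.282) × √(2/640) = 0.216, about 0.22 SD.
- Total for 90% power at 0.15 SD: 2 × 1,325 / 0.10 / 0.8 = 33,125.
- Share of index persons with ILI needed for 90% power at 16,000: 2 × 1,325 / (16,000 × 0.8) = 20.7%, about twice the stated minimum.

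**Reading B: days per index person, zero for those not ill.**
- All followed-up index persons count: 16,000 × 0.8 / 2 = 6,400 per group. No 24% (or 10%) divisor applies.
- If 0.15 SD is meant on this scale, power exceeds 99.9%.
- But 0.15 SD among ill persons is not 0.15 SD on this scale. For illustration, assume 10% ill, an effect only through shorter illness, and an SD-to-mean ratio of duration among the ill between 0.5 and 1.0 (not given in the protocol). The effect is then 0.022 to 0.034 SD over all index persons, with power of 9% to 26%. Fewer episodes would add to this. The example shows only that the scale must be stated.

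**Result.** The 24% fits neither reading.

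**The case against.** The strongest objection is that 54% depends on an analysis set that the protocol never fixes. Its hypothesis in 3.9 and 3.10 is that fewer episodes lead to fewer symptomatic days. The analysis is by intention to treat, and 3.11 costs each symptom day prevented. All of this fits days per randomised person. Restricting to ill persons would condition on an event that the intervention is meant to change. This stands: 54% is conditional. On the other side, duration is recorded per episode, 3.1 lists duration of ILI as an outcome, and the footnote speaks of days due to an illness. Neither reading can be ruled out, and 13,802 is wrong on both.

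Second, the cell is not a bold target and does not set the sample size, and the power claim stands in the passage on RTIs. The first part is right and limits the consequence. The second is weaker, because the clause covers continuous outcomes without restriction and points to a table with an ILI column.

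Third, 10% is a minimum, the 0.2 SD of the footnote has 84% power, and confidence intervals will be reported. All true. They soften the consequence without making the 24% right.

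A reader might infer that the trial is too small, that 33,125 patients should be enrolled, or that ILI duration should lose its primary status. The documents support none of these. The 16,000 rests on ILI transmission, where the 24% is the basis the plan intends, and 33,125 applies only under Reading A.

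**Conclusion.** Wrong as written; minor. The ILI total of 13,802 in the continuous-outcome row rests on a household transmission share, while the main symptom analysis is in the index person.

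The size depends on the analysis set. With ill index persons only, and on the table's own alpha and loss and the 10% minimum, power at 16,000 is about 54% for 0.15 SD where the table implies 94%. A higher ILI share would raise it. With zeros included, the cell should carry no 24% divisor, and power cannot be judged until the effect is defined on that scale.

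The bold targets of 3,314 for days of illness in all RTIs and 15,074 for ILI transmission are not touched. An unconditional statement that ILI duration has 54% power would go beyond the protocol.

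**What to change.** In Protocol 3.12:
- State beside the continuous row whether ILI days are analysed in index persons who had ILI, or per index person with zero for those not ill.
- Replace or remove 13,802 to match. With ill index persons only, the total for 0.15 SD at 90% power is 33,125, given for reference and not as a recruitment target. With zeros, drop the 24% divisor and define the effect size over all index persons.
- Give the effect detectable at 16,000: about 0.22 SD at 90% power if only ill index persons are analysed.
- Limit the strong power statement for continuous outcomes to days of illness for all RTIs.

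The cost is one table cell and a few sentences, and under Reading A a less favourable power figure. Enrolment and the outcome hierarchy stay as they are.

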
#### Range of effect sizes likely for the trial (bold= our target for that outcome)

| Effect size                                                                                                               | N per group
(with complete outcomes where
transmission of infection possible
either to or from the index person) | Total N required for ILI
(assuming 24% where transmission
possible to or from index person; and
allowing for 20% loss to follow-up) | Total N for all respiratory
infections (assuming all cohort where
transmission possible; and allowing
20% loss to follow-up) |
|---------------------------------------------------------------------------------------------------------------------------|---------------------------------------------------------------------------------------------------------------------------|----------------------------------------------------------------------------------------------------------------------------------------------|---------------------------------------------------------------------------------------------------------------------------------------|
| Dichotomous outcomes e.g. transmission
(alpha=0.05 beta=0.2)                                                   |                                                                                                                           |                                                                                                                                              |                                                                                                                                       |
| 20% vs 18% (NNT 50; OR 0.88)                                                                                       | 6039                                                                                                                      | 62,906                                                                                                                                       | 15,098                                                                                                                         |
| 20% vs 17% (NNT 33; OR 0.82)                                                                                              | 2629                                                                                                                      | 27,386                                                                                                                                       | 6574                                                                                                                                  |
| 20% vs 16% (NNT 25 OR 0.76)                                                                                        | 1447                                                                                                                      | 15,074                                                                                                                                | 3618                                                                                                                                  |
| 20% vs 15% (NNT 20 OR 0.71)                                                                                               | 906                                                                                                                       | 9,438                                                                                                                                        | 2266                                                                                                                                  |
| Continuous outcomes e.g. days illness
(alpha=0.01 (multiple outcomes); beta=0.1)
standardised effect sizes |                                                                                                                           |                                                                                                                                              |                                                                                                                                       |
| 0.15                                                                                                                      | 1325                                                                                                                      | 13802                                                                                                                                        | 3314                                                                                                                           |

\* standardised effect size of 0.2 = one day or less of moderately bad symptoms due to ILI or RTI

**3.13 What is the planned recruitment rate?** We will utilise the English Primary Care Research Network (PCRN) to aid with recruitment and retention. We propose recruiting this cohort over 18 months with 1 year of follow-up; this is based on our previous experience that recruiting using this mechanism 1000-1100 patients per practice should agree in under one year; 18 months will provide sufficient leeway to ensure recruitment occurs. In each practice if fewer than expected agree it will be relatively easy to select and invite more patients.

**3.14 Are there likely to be any problems with compliance?** We already have good reason to believe that patients are likely to comply, and that a trial of this size will probably find an effect; effect sizes should be larger with better development, tailoring and an interactive website.

**3.15 What is the rate of loss to follow-up?** 20% - based on our previous trials e.g. MRC ATEAM.

**3.16 How many centres will be involved?** Two centres and their local Networks (Birmingham, Southampton).

**3.17-.18. Data Entry, analysis.** Data forms will be scanned from pre printed sheets as in our previous study.

**Main trial analysis.** The data will be analysed according to the Statistical Analysis Plan which will be approved by the Trial Steering Committee before the commencement of any analysis. One intention to treat analysis will be performed. We will assess the transmission of ILI or other respiratory tract infection - i.e. either between the index case and family members or from family members to the index person - using multiple logistic regression, the duration of symptoms labelled moderately bad days using multiple linear regression, and attendance at the GP surgery using Poisson regression, controlling for stratifiers. We found in our previous trial of leaflets there were no significant clustering effects by practice; our analysis will be based on the index patient to avoid a design effect due to family clustering. For the symptom data the main analysis will be of symptoms in the index person but a secondary analysis will assess symptoms reported for all other family members averaged at the level of the family. Confidence intervals will be reported, and the study will be reported in accordance with the CONSORT statement.

**Subgroup analysis (using two sided 1% significance levels).** We will assess whether any of the stratification variables are effect modifiers; whether age, deprivation, education level, and co-morbidities predict outcomes or are effect modifiers; whether self reported adherence to each behaviour determines outcome.

**Diagnostic study analysis.** We will assess the sensitivity specificity likelihood ratios and positive and negative predictive values for symptoms and temperature in the whole sample, and in the sub-samples who would not contact their practice or NHS Direct (either in this or in past episodes). We will use logistic regression to determine which symptoms (and or temperature) individually or in combination are most predictive. We will also estimate the predictive value of symptoms (and or temperature) for laboratory diagnosed influenza at 12 hours after the start of the illness, then at 24 hours, 36 hours, 48 hours, and 48+ hours.

**3.20 Has a pilot study been carried out?** We have not piloted this precise protocol, but have recruited very similar trial cohorts using similar recruitment mechanisms, and have developed similar websites

